## Abstract

**Introduction::**

Chronic prostatitis (CP) is a common genitourinary disorder in adult men. It has a high incidence, a complex disease, and a lingering course, which seriously affects the quality of life of patients. For the treatment of CP, the currently available treatment methods are limited and patients are not satisfied with the treatment results. Therefore, more effective treatment options need to be further explored.

**Methods::**

The study is a single-blind, parallel-group, randomized controlled clinical trial consisting of a 4-to-6-week treatment period and a 6-month follow-up period. Included participants will be randomized into three groups and given a treatment regimen of acupuncture, qianliean suppository, respectively. Patients in each group will be treated for 1 month as a course of treatment. The clinical efficacy and changes in inflammatory factor levels in each group will be assessed at the end of treatment.

**Discussion::**

The trial aims to promote a more effective, standardized, and efficacious treatment protocol for CP in the clinical setting.

## Introduction

1

Chronic prostatitis (CP) is the most common genitourinary disorder in adult men. Surveys have shown that 35% to 50% of men will be affected by prostatitis at some point in their lives.^[1]^ CP is a difficult class of disease to treat. The typical clinical presentation of the disease is prolonged and recurrent pain in the pelvic region. The duration of the painful discomfort is often greater than 3 months. Some patients also often have varying degrees of urinary symptoms and sexual dysfunction.^[2,3]^ CP is a complex and protracted disease, which is difficult to treat. It brings serious psychological and economic burdens to patients and seriously affects their quality of life. Some patients even develop severe anxiety and depression as a result, which in turn leads to many social problems. Currently, it has attracted the attention of clinicians in various countries. In recent years, Western medical treatment of CP has gradually changed from antibiotics to a combination of α-blockers, androgens, anti-anxiety and antidepressants, and the efficacy has improved, but patients are still not satisfied with the treatment effect.^[4]^ Therefore, it is often necessary to continuously increase the dose of medication in order to achieve a more satisfactory therapeutic effect. This may cause serious adverse effects and affect patient compliance with treatment. Based on the above status, more effective treatment modalities need to be further explored.^[5]^ As a traditional treatment modality inherited for thousands of years, acupuncture has been valued and widely used in the clinical treatment of CP in recent years.^[6]^ This treatment modality can improve the quality of life by promoting neuromuscular excitability and by enhancing the contractility of urethral muscles and perineal muscles. qianliean suppository is a topical preparation made from several Chinese herbs with the effects of clearing heat, relieving dampness, promoting laxity, resolving siltation, dispersing nodules, and relieving pain. This study will investigate the therapeutic effects of acupuncture combined with qianliean suppository on CP, aiming to provide valuable evidence-based medical evidence for clinicians.

## Methods

2

### Study design and setting

2.1

The study is a single-blind, parallel-group, randomized controlled clinical trial consisting of a 4- to 6-week intervention and a 6-month follow-up period. The study will be conducted at one site, the Affiliated Hospital of Shaanxi University of Chinese Medicine. A brief flow chart of the entire study is shown in Figure 1. This study will adopt a parallel controlled design approach. We will ensure a balance of baseline data across groups by having an adequate sample size and a completely randomized grouping method. The study will be approved by the Ethics Committee of the Affiliated Hospital of Shaanxi University of Chinese Medicine. We will not begin recruiting participants until ethics committee approval has been obtained.

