#### Eligibility criteria

2.2.2

The inclusion criteria for participation are as follows:(1) Patients who mEet the diagnostic criteria for CP; (2) Patients who have a medical history of at least 3 months and are not on the appropriate treatment medication within 2 weeks prior to admission; (3) Patients who voluntarily participate in this study and signe an informed consent form. (4) Patients should be between the ages of 18 and 50 years; (5) Patients can receive emails and cell phones can receive text messages.

The exclusion criteria are as follows:(1) patients with combined severe neurological dysfunction, urethral stricture, prostate tumors; (2) patients with a history of pelvic surgery; (3) patients with combined severe cardiovascular disease, cerebrovascular disease, hepatic and renal insufficiency, hematopoietic system disease, and neurological disease; (4) patients with allergic reactions to drugs and psychiatric disorders.

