#### Primary outcome measure

2.5.1

The CP symptom index (NIH-CPSI) with prostatitis-related sexual function index score will be performed before and after treatment. The changes of urodynamic indexes will be observed in each group before and after treatment, and the specific indexes included maximum urinary flow rate, maximum bladder capacity, maximum forced urinary muscle pressure and bladder stability. The observation times for the primary outcome indicators are shown in Table 1.

**Table 1 T1:** Treatment schedule and outcome measures.

Items	Before Treatment	Treatment period, twice a week, 8 times in total (treatment starts within 1 wk after registration)				Post observation Period
TIME POINT	Registration	wk 1	wk 2	wk 3	wk 4	1 wk later Treatment completion
Inclusion criteria	√					
Exclusion criteria	√					
Informed consent	√	√	√	√	√	√
Confirmation of subjective symptoms	√		√		√	√
Chronic prostatitis symptom index	√	√	√	√	√	√
prostatitis-related sexual function index Observation of adverse events	√		√		√	

Clinical efficacy evaluation criteria: significant effect: the symptoms of urinary disorder disappeared after treatment, no pain and discomfort, and normal sexual function will be restored at the same time; effective: the symptoms of urinary disorder basically disappeared, a little pain and discomfort existed, pain will be tolerated, and sexual function will be basically restored to normal; ineffective: the situation of urinary disorder did not improve, obvious pain and discomfort existed, and no significant change in sexual function will be seen. The total effective rate =  (the number of effective cases to the number of effective cases)/total cases × 100%.

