For the treatment of this disease, the common treatment options can be divided into pharmacotherapy (α-blockers, antibiotics, analgesics and botanicals), physiotherapy (biofeedback, microwave therapy, acupuncture) and surgery. Several randomized controlled trials and Meta-analyses have shown acupuncture to be effective in CP^[11–13]^ and a relatively safe treatment. Studies have shown that acupuncture can improve patients’ symptoms, reduce patients’ NIH-CPSI scores and decrease the number of white blood cells.^[14]^ However, there is still a lack of systematic and comprehensive clinical studies on acupuncture for the treatment of this disease, and most trials lack follow-up to understand the long-term efficacy. Therefore, this study will objectively evaluate the short-term and long-term clinical efficacy of different treatment regimens and the effect on the level of inflammatory factors in the organism by designing a standardized clinical trial with an acupuncture group and a Qianliean suppository group with NIH-CPSI scale score as the main outcome index, combined with a long follow-up. This study hopes to provide more ideas for the clinical treatment of CP.

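### A 6-month follow-up and a long-term efficacy aim are stated, but no outcome is dated later than 1 week after treatment

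*Protocol article*

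**What the plan says.** The Abstract (Methods) describes a trial "consisting of a 4-to-6-week treatment period and a 6-month follow-up period", and section 2.1 repeats it almost word for word: "consisting of a 4- to 6-week intervention and a 6-month follow-up period". The Discussion gives the follow-up a purpose. It faults most earlier acupuncture trials for lacking follow-up and states that "this study will objectively evaluate the short-term and long-term clinical efficacy of different treatment regimens", with the NIH-CPSI score as the main index.

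Section 2.5.1 is where the timing is set: "The observation times for the primary outcome indicators are shown in Table 1". Table 1 has a registration column, four weekly columns headed "Treatment period, twice a week, 8 times in total", and a single post-treatment column, "1 wk later Treatment completion". The NIH-CPSI row is ticked in all six.

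The other timing statements are consistent with this:

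- The text of 2.5.1 says that the NIH-CPSI and sexual function scores "will be performed before and after treatment", and times the urodynamic indices likewise.
- Section 2.5.2 times the blood samples for inflammatory factors in the same way.
- The Abstract places the assessment of efficacy and inflammatory factors at the end of treatment.
- Section 2.7 plans a repeated-measures analysis of NIH-CPSI over several time points without naming them.

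**The concern.** The follow-up length and the schedule do not agree. The trial gives durability of effect as a reason for its design, yet the table that fixes the primary-outcome times stops shortly after the last treatment session. The article describes the pain of chronic prostatitis as prolonged and recurrent, so a score taken 1 week after treatment says little about whether a benefit lasts.

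If the schedule is followed as printed, any statement about long-term efficacy would rest on that 1-week value, and the trial would repeat the gap that its Discussion criticises in earlier work. Scores not collected at later months cannot be recovered once those months have passed.

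**Working it through.** No sample size or power figure bears on this point. The check sets the stated follow-up against every outcome time in the document and counts the weeks left uncovered.

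**Inputs**

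- Follow-up: 6 months (Abstract; section 2.1), taken as about 26 weeks.
- Treatment span in Table 1: weeks 1 to 4.
- Last column of Table 1: 1 week after completion.
- Treatment starts within 1 week of randomization (section 2.2.3).
- Start of the 6 months: not stated, so both readings are shown.

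**Last dated assessment:** 4 + 1 = about week 5 from the start of treatment.

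**Reading A, follow-up runs from the end of treatment**

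- Uncovered weeks = 26 − 1 = 25.
- Share = 25/26 = about 96%.

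**Reading B, the 6 months run from randomization**

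- Treatment starts at once: 26 − 5 = 21 weeks, 21/26 = about 81%.
- Treatment starts 1 week later: 26 − 6 = 20 weeks, 20/26 = about 77%.

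Reading B uses the four treatment weeks of Table 1. The Abstract and section 2.1 allow 4 to 6 weeks, while section 2.4 gives 1 month. With six weeks of treatment, Reading B would leave 26 − 7 = 19 or 26 − 8 = 18 weeks, and Reading A would not change. These statements of treatment length also need reconciling, because the end of treatment is one possible start of follow-up.

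**Side by side**

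| Place | Outcome timing given | Dated point later than 1 week after treatment? |
|---|---|---|
| Abstract | End of treatment | No |
| 2.5.1, text | Before and after treatment | No |
| 2.5.1, Table 1 | Registration, weeks 1 to 4, 1 week after completion | No |
| 2.5.2 | Before and after treatment | No |
| 2.7 | Several unnamed time points | Not stated |
| Figure 1 | Not shown | Unknown |

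On either reading, most of the follow-up has no dated efficacy measurement.

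**The case against.** **The follow-up is not wholly empty.** A reader might infer that it yields no outcome data at all. The document does not support that: Table 1 ticks NIH-CPSI and subjective symptoms 1 week after completion, which lies inside a follow-up counted from the end of treatment. What stands is that nothing is dated after that visit.

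**Table 1 is incomplete in other respects.** The urodynamic indices, listed as primary outcomes, have no row, and neither do the inflammatory factors. Nobody would conclude from this that they go unmeasured, so the table's silence alone does not prove that month-6 scores will not be collected. This limits the point to a conflict within the document. It does not remove it, because NIH-CPSI does have a row and section 2.5.1 names the table as the source of its times.

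**Some material is unseen.** Figure 1, the flow chart of the whole study, might mark later visits, and a journal article condenses a fuller protocol. But the article does not leave the timing to another document; it sets the times in Table 1. A later visit in Figure 1 would itself conflict with that table.

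**Section 2.7 does not exclude follow-up.** This is correct. Its unnamed time points neither include nor rule out later months, so it cannot be said that the analysis plan omits them.

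**Long-term efficacy may not be a principal question.** A reader might count it as one of two stated questions of the trial. The document does not say so. The Introduction's aim is the therapeutic effect of the combination, and long-term efficacy appears as an aim in one Discussion sentence that also lists inflammatory factors. It is a stated aim, but its rank is not given.

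**Conclusion.** The point holds as an internal contradiction. The document states a 6-month follow-up and a long-term efficacy aim on NIH-CPSI, while its own schedule dates no assessment beyond 1 week after treatment. About 25 of 26 weeks are uncovered if follow-up starts at the end of treatment, or about 20 to 21 weeks if it starts at randomization with the four-week treatment span of Table 1. The figure of 96% belongs to the first reading only and should not be quoted without it.

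As scheduled, long-term efficacy cannot be assessed. The end-of-treatment comparison, which is the assessment that the Abstract names, is unaffected. The conclusion rests on the visible text, with Figure 1 not shown. The conflict should be settled before any patient reaches the follow-up period.

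**What to change.** Reconcile section 2.1, the Abstract, Table 1 and the Discussion in one of two ways.

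**Keep the long-term aim.**

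- Add dated NIH-CPSI assessments through month 6 to Table 1. Months 1, 3 and 6 are one possible choice.
- State when the follow-up starts.
- Use remote questionnaires where feasible. The inclusion criterion "Patients can receive emails and cell phones can receive text messages" helps with contact, but it shows only that messages can be received, not that questionnaires will be returned.
- Record any other treatment for chronic prostatitis used during follow-up.
- Name the between-group comparison of NIH-CPSI at month 6 as a secondary analysis, and include the added time points in the repeated-measures model already planned in section 2.7.
- State how missing month-6 values are handled. Section 2.6 carries the last observation forward for patients whose treatment course is incomplete and gives no rule for follow-up. Carrying an early score to month 6 would assume the durability that is being tested.

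**Or drop it.** Delete the 6-month follow-up and every long-term efficacy claim.

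The first option costs an amended table, about three questionnaires per patient on the example schedule, a few lines of analysis text and some attrition to report. The second costs wording only, but gives up the long-term aim.

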**Figure 1 F1:**
[figure not shown]
Study design flow chart.

### Participants

2.2

#### Diagnostic criteria of CP

2.2.1

The diagnostic criteria for this study will be developed with reference to s *Wu Jieping Urology (2013 edition)*.^[7]^ The specific criteria are as follows:

(1)Symptoms: They are divided into two aspects. On the one hand is the symptom of irritation in the lower urinary tract, and the other is the symptom of inflammatory reaction or reflex pain. The symptoms are varying degrees of urinary frequency, urgency, painful urination, incomplete urination, and burning in the urethra. There is occasionally a small amount of white discharge from the urethra in the morning, at the end of urination or during bowel movements. Pain and swelling in the perineum, external genital area, lower abdomen, suprapubic area, lumbosacral and perianal areas.(2)Prostate palpation: texture: full gland, or soft and hard, or inflammatory nodules, or tough texture. Pressure pain: there may be limited pressure pain. Size: can be enlarged, normal or reduced.(3)Prostate fluid (EPS) Microscopy: WBC 10/HP; lecithin vesicles reduced or absent.(4)Bacterial culture of prostatic fluid (EPS): negative bacterial culture.(5)Ultrasonography: Ultrasound image is obviously abnormal: manifesting as normal or reduced prostate size, uneven internal echogenicity, visible enhanced light spots and nodal echogenicity, enhanced, thickened and rough peritoneal echogenicity. The ultrasound image is mildly abnormal; it shows normal or slightly enlarged prostate size, slightly strong or weak internal echogenicity, and poorly defined periosteal echogenicity.

The diagnosis of CP can be made by having (1) and (2) above, and other tests can be performed according to the patient's specific situation.

#### Eligibility criteria

2.2.2

The inclusion criteria for participation are as follows:(1) Patients who mEet the diagnostic criteria for CP; (2) Patients who have a medical history of at least 3 months and are not on the appropriate treatment medication within 2 weeks prior to admission; (3) Patients who voluntarily participate in this study and signe an informed consent form. (4) Patients should be between the ages of 18 and 50 years; (5) Patients can receive emails and cell phones can receive text messages.

The exclusion criteria are as follows:(1) patients with combined severe neurological dysfunction, urethral stricture, prostate tumors; (2) patients with a history of pelvic surgery; (3) patients with combined severe cardiovascular disease, cerebrovascular disease, hepatic and renal insufficiency, hematopoietic system disease, and neurological disease; (4) patients with allergic reactions to drugs and psychiatric disorders.

#### Recruitment

2.2.3

The study will be open to participants from all regions of China. Participants can enroll through the hospital's official website or be referred to our specialty clinics by healthcare professionals. The study will be promoted to healthcare providers, patient organizations, and directly to the public through the website and social media. We will also advertise in digital media. Participants will be assigned a screening ID and a member of the study team will conduct the initial eligibility screening. If they are interested in participating and potentially eligible, participants will be booked for the assessment. The inclusion assessment will be conducted under the supervision of a clinician. Additional information about the study will be provided immediately following this assessment. The assessor will perform final verification of the participant's eligibility criteria and sign the informed consent form. If the assessor is unsure of the eligibility of a potential participant, the principal investigator will have the final say. After signing the informed consent form, participants will be assigned a new study ID and will be randomized to a group. Treatment will begin within 1 week of randomization grouping. Where possible, excluded participants who still require clinical attention will be given routine treatment. Screening IDs and reasons for exclusion will be recorded for use in the final study report.

### Randomization, allocation concealment, and blinding

2.3

The randomization system used for this study will be provided by the Affiliated Hospital of Shaanxi University of Chinese Medicine. Eligible patients will be identified by the treating physician based on inclusion and exclusion criteria. Participants will be referred to a study coordinator who will randomly assign them to each group. The randomization list will be kept by the statistician and study coordinator until the end of the study to ensure allocation concealment.

### Interventions

2.4

(1)Acupuncture group: selected acupoints: *Shensu, Zhongliao, Huiyang, and Sanyinjiao* (all taken bilaterally). The acupuncture points will be positioned with reference to the 2006 National Standard of the People's Republic of China (GB/T 12346–2006) “Name and Positioning of Acupuncture Points”. After local sterilization of the acupoints, Shensu and Sanyinjiao will be needled with 0.3 × 40 mm milli-needles at a depth of 20 to 30 mm; Zhongliao and Huiyang will be needled with 0.3 × 75 mm milli-needles at a depth of 50 to 70 mm; the needles will be retained for 30 minutes.(2)Qianliean suppository group: use prostate suppository (National Drug Administration Z10980066, specification 2g × 5 s) for treatment. This product is brown or black-brown torpedo type suppository. Usage: The drug is inserted into the anus at night before bedtime, placed at a depth of 2 cm, 1 capsule each time, once a day. The ingredients of this drug are: extracts of Chinese herbs such as *Huangbai, Huzhang, Zhizi, Dahuang, Zelan, Maodongqing, Wuzhuyu, Weilingxian, Shichangpu and Lizihe*. Precautions for use: After the suppository is inserted into the anus, if there are uncomfortable symptoms such as bowel movement, abdominal pain and diarrhea, the method of use can be improved, such as applying vegetable oil outside the suppository or placing the suppository deeper, after the rectum adapts, the above symptoms can be reduced or disappear.(3)Combination therapy group: The treatment methods of (1) and (2) are combined.

Patients in each of the above groups will be treated for 1 month as a course of treatment. Patients in each group will be asked to abstain from sexual intercourse during the treatment period, to ensure the cleanliness of the perineal area, to observe the adverse reactions and to provide timely and effective treatment to ensure the treatment effect.

### Outcome measures

2.5

#### Primary outcome measure

2.5.1

The CP symptom index (NIH-CPSI) with prostatitis-related sexual function index score will be performed before and after treatment. The changes of urodynamic indexes will be observed in each group before and after treatment, and the specific indexes included maximum urinary flow rate, maximum bladder capacity, maximum forced urinary muscle pressure and bladder stability. The observation times for the primary outcome indicators are shown in Table 1.

**Table 1 T1:** Treatment schedule and outcome measures.

Items	Before Treatment	Treatment period, twice a week, 8 times in total (treatment starts within 1 wk after registration)				Post observation Period
TIME POINT	Registration	wk 1	wk 2	wk 3	wk 4	1 wk later Treatment completion
Inclusion criteria	√					
Exclusion criteria	√					
Informed consent	√	√	√	√	√	√
Confirmation of subjective symptoms	√		√		√	√
Chronic prostatitis symptom index	√	√	√	√	√	√
prostatitis-related sexual function index Observation of adverse events	√		√		√	

Clinical efficacy evaluation criteria: significant effect: the symptoms of urinary disorder disappeared after treatment, no pain and discomfort, and normal sexual function will be restored at the same time; effective: the symptoms of urinary disorder basically disappeared, a little pain and discomfort existed, pain will be tolerated, and sexual function will be basically restored to normal; ineffective: the situation of urinary disorder did not improve, obvious pain and discomfort existed, and no significant change in sexual function will be seen. The total effective rate =  (the number of effective cases to the number of effective cases)/total cases × 100%.

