### Statistical analyses

2.7

The case information collected by Excel will be imported into SPSS 25.0 statistical software to establish the analysis database and complete the statistical analysis of the data. Normality test will be performed by Kolmogorov-Smirnov method; chi-square test will be performed by Levene method. The measurement data conform to normal distribution and will be described by means and standard deviations, and comparisons between groups will be made by one-way ANOVA ANOVA or independent samples *t*-test; two-way comparisons will be made by Bonferroni method corrected *P*-value; not conforming to normal distribution, the measurement data will be described by medians and quartiles, and comparisons between groups will be made by Kruskal-Wallis method test or The Mann-Whitney *U* test will be used for comparison between groups, and the Dunnett's method will be used for comparison between two groups. The dichotomous data will be expressed as composition ratio and frequency in describing the distribution pattern, and the chi-square test and exact Fisher test will be used for comparison between groups. NIH-CPSI scores, mean urine flow rate and maximum urine flow rate will be compared between the two groups of patients at different time points using repeated measures ANOVA-generalized linear model equations.

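### Section 2.5.1 gives six or seven measures primary status while the Discussion puts NIH-CPSI first, and no visit is named as the primary analysis time

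*Protocol article*

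**What the plan says.** All references are to the protocol article.

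- **Section 2.5.1, two scores:** "The CP symptom index (NIH-CPSI) with prostatitis-related sexual function index score will be performed before and after treatment".
- **Section 2.5.1, urodynamics:** "The changes of urodynamic indexes will be observed in each group before and after treatment". Four such indexes are named, covering peak flow, bladder capacity, peak pressure and bladder stability. The section then refers to these measures in the plural as primary and sends the reader to Table 1 for their times.
- **Section 2.5.1, after Table 1:** efficacy categories are set out and summarised as a responder proportion ("The total effective rate"). The text does not itself call this primary. Section 2.5.2 lists only serum inflammatory factors as secondary.
- **Discussion:** the trial is described as designed "with NIH-CPSI scale score as the main outcome index, combined with a long follow-up".
- **Section 2.7:** pairwise comparisons between groups are corrected (Bonferroni, or Dunnett's method for non-normal data). For the repeated-measures analysis, "NIH-CPSI scores, mean urine flow rate and maximum urine flow rate will be compared".
- **Table 1:** NIH-CPSI is collected at registration, weeks 1 to 4, and 1 week after completion. Treatment is "twice a week, 8 times in total (treatment starts within 1 wk after registration".
- **Section 2.1:** the trial is described as "consisting of a 4- to 6-week intervention and a 6-month follow-up period". Section 2.4 gives the course as one month.

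**The concern.** The primary outcome fixes which result is confirmatory. Here two places define it differently: section 2.5.1 gives several measures equal standing, and the Discussion puts one of them first. A statistical analysis plan written from this text would have no single primary outcome to implement.

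Three further gaps make this worse. No visit is chosen for the primary comparison. The measures in section 2.5.1 do not match the times in Table 1 or the variables in section 2.7. The treatment length is stated in three ways, so a visit defined by the end of treatment has no fixed distance from randomisation. Left as it is, the choice of deciding outcome and visit could be made after the results are seen, and the nominal error rate would then not describe the claim.

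**Working it through.** **1. Count of outcomes under the primary heading.** NIH-CPSI and the sexual function index make 2. Maximum flow rate, maximum bladder capacity, maximum pressure and bladder stability make 4. So 2 + 4 = 6 measures are explicitly treated as primary. The total effective rate makes 7, but only by its position under the heading.

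**2. The passages side by side.**

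| Measure | Section 2.5.1 | Table 1 (as extracted) | Repeated measures, 2.7 | Discussion |
|---|---|---|---|---|
| NIH-CPSI | listed | registration, weeks 1–4, 1 week after completion | yes | leading outcome |
| Sexual function index | listed | registration, weeks 2 and 4 (row merged with adverse events) | not named | not named |
| Maximum flow rate | listed | no row | yes | not named |
| Other three urodynamic indexes | listed | no row | not named | not named |
| Total effective rate | under the heading | no row | not named | not named |
| Mean flow rate | not listed | no row | yes | not named |

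The four places do not agree on one set of outcomes. NIH-CPSI is the only measure that appears in all of them.

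**3. Primary time.** NIH-CPSI has five collection times after baseline, and none is marked as primary. A comparison before and after treatment could mean week 4 or the visit 1 week after completion. The Discussion also links NIH-CPSI to a long follow-up, yet Table 1 as extracted has no 6-month column.

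**4. Where the last Table 1 visit could fall.** Section 2.2.3 allows up to 1 week from randomisation to the start of treatment. With the 4- to 6-week intervention of section 2.1:
- earliest: 0 + 4 + 1 = 5 weeks after randomisation;
- latest: 1 + 6 + 1 = 8 weeks after randomisation.

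**5. Illustrative error rates.** The article states no alpha, power, effect size or sample size, so there is no figure of its own to reproduce. Assumptions: two-sided 5% per outcome; no effect on any outcome; success claimed if any one outcome is significant.

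Independent outcomes, 1 − 0.95^k:
- k = 6: 1 − 0.95^6 = 0.265
- k = 7: 1 − 0.95^7 = 0.302

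Equally correlated outcomes, by simulation of k two-sided z-tests (400,000 draws):

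| Correlation | 6 outcomes | 7 outcomes |
|---|---|---|
| 0.3 | 0.241 | 0.271 |
| 0.5 | 0.207 | 0.229 |
| 0.7 | 0.164 | 0.178 |
| 0.9 | 0.108 | 0.116 |

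The Bonferroni correction over the three pairs of arms does not remove this. Seven outcomes with three contrasts each are 21 tests at 0.05/3, and 1 − (1 − 0.05/3)^21 = 0.297 if the tests are independent.

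A free choice among the five NIH-CPSI times alone would give 0.183 at correlation 0.5 and 0.101 at correlation 0.9, under the same kind of assumption.

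**The case against.** - **Any outcome can win.** A reader might infer that the trial may claim success on any of the listed measures. No such rule is written. If every primary outcome had to succeed, the familywise error would be at or below 5%. What stands is that no rule of either kind is given.
- **The error rates.** They rest on an assumed alpha, assumed correlations and an assumed any-one rule, so it would be wrong to say that this trial's false-positive risk is several times 5%.
- **The count of seven.** This is the high reading, because the effective rate is never called primary. Six is the firm count.
- **The Discussion.** It gives NIH-CPSI the lead, which need not mean it is the sole primary outcome. The same sentence names only two of the three treatment groups, so it is loosely written. It still differs from section 2.5.1, which ranks nothing.
- **Unfixed times.** It is tempting to say that the times are open. For NIH-CPSI the collection times are fixed in Table 1, and what is open is which of them is primary. The missing urodynamic row could in part be damage from text extraction, since one row of the table is visibly merged.
- **Detail left to an analysis plan.** Multiplicity rules are often placed there, and that plan is not shown. Their absence alone would not be a finding. The conflict between section 2.5.1 and the Discussion, and the flow variable in section 2.7 that 2.5.1 does not list, are printed in the article and would not be excused by a later plan.

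**Conclusion.** The point holds as a stated contradiction about which result decides the trial, and it must be resolved. Six measures are treated as primary, or seven by placement, against one leading outcome in the Discussion. No hierarchy, co-primary rule or alpha split is stated across outcomes, and no primary analysis visit is named. The mismatches with Table 1 (as extracted) and with section 2.7 add to this.

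The consequence can only be illustrated. At an assumed 5% per outcome with any one success claimed, the chance of a false positive runs from 26.5% (six) or 30% (seven) with independence down to about 11–12% at correlation 0.9. These are not properties that the document gives the trial. The spread of about 5 to 8 weeks for the last Table 1 visit applies if the 4- to 6-week statement governs and treatment starts anywhere within the permitted week.

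**What to change.** - In section 2.5.1, make the change in NIH-CPSI total score from baseline to one named visit the only primary outcome. Set that visit at the same time since randomisation in all three arms. This is in line with the emphasis in the Discussion.
- Move the sexual function index, the urodynamic indexes and the effective rate to secondary, without confirmatory claims. If several primary outcomes are kept instead, state whether all must succeed or how alpha is split; an equal Bonferroni split would be 0.05/6 = 0.0083 or 0.05/7 = 0.0071 per outcome at an assumed overall 5%.
- Give the urodynamic times in Table 1, and make the flow variables in section 2.7 match section 2.5.1.
- Reconcile the three statements of treatment length (4 to 6 weeks; one month; 4 weeks with 8 sessions). This review does not say which is right.

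The cost is mainly protocol wording, plus scheduling if the urodynamic visits are not already planned. The downside is that the other outcomes could no longer carry the trial's claim on their own.
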